#### Assessment

There are three assessments: Baseline/Time 1, prior to intervention; Time 2, 20 weeks post baseline; and Time 3, 52 weeks post baseline. All assessments are being conducted by an experienced clinician blinded to group allocation.

*Baseline measures* include socio-demographic data (age, sex, ethnicity, pension status, health insurance, education) and clinical data (health and cognitive conditions, medications). The Addenbrooke’s Cognitive Examination Third edition (ACE-III) [38] and the GDRS [2] are being used to record cognitive function and dementia severity. Following baseline assessment, participants are randomised to either the intervention or the control group.

*Outcome measures* consist of primary and secondary outcomes. The primary outcome is the client’s functional independence at Time 2, assessed using the Disability Assessment for Dementia (DAD) [1] which measures self-care disability and independent living skills. Secondary outcomes are: self-care disability and independence at Time 3; both short- and long-term effects on mobility and physical function, health-related quality of life, carer burden, carer quality of life, and home environmental safety; and total health care costs over the 52 weeks following randomisation. The secondary outcome measures are:Short Physical Performance Battery (SPPB) [39] for objective physical functionCollateral Source version of the Geriatric Depression Scale-15 item (CS-GDS-15) [40] for depressionQuality of life in Alzheimer’s disease (QOL-AD) [41, 42] for general quality of life5-Level version of the EuroQol five dimensions (EQ-5D-5 L) [43, 44] for health-related quality of life (both client and carer) for the economic evaluation, using the Australian weighting algorithm [45]Zarit Burden Inventory (ZBI) [46] for carer burdenThe Home Safety Self-Assessment Tool (HSSAT) for the overall home environment safety.

In addition, monthly telephone contact is made with all carers to monitor participants’ use of prescribed medicines and costs associated, healthcare and community services (type, duration and frequency, and personal costs), incidents of falls and minor injuries as well as carers’ workforce participation (i.e. total number of work hours in the last week). To ensure accurate recording, carers are given a diary/log to complete and during the monthly phone call this is verified. This method was used successfully in the I-HARP pilot.

##### Implementation process evaluation

Multiple sources of data are being collected including:case/clinical notes and field notes from I-HARP clinicians and case coordinators;I-HARP related administrative data and case audit for each of the four research sites;interviews with all consenting study participants after Times 2 and 3 data collection, providing further accounts of their experiences with reablement approaches to care either as I-HARP participants or as control group participants in their usual care (n ≈ 100); andfocus group interviews with I-HARP interventionists and key managers of the participating research sites after Time 2 data collection, providing perspectives of the participating organisations and interventionists on reablement approaches to care for people living with dementia and I-HARP processes, and mechanisms of their decision making (4 focus groups, 1 per site, with 4–6 people per group).

All interviews are conducted in a combination of semi-structured and structured form designed specifically for the I-HARP evaluation. Both clients and carers are invited to be interviewed individually. The interviews with study participants take about 45–60 min and are conducted face-to-face at home or via telephone, depending on their preference. The focus group interviews will take about 1–1.5 h and be conducted face-to-face at each participating research site. For the focus groups, the participants will be given opportunity to provide further comments to the research team if they have not been able to voice their concerns or issues during the group discussion.

#### Randomisation, allocation concealment, and blinding

After recruitment to the study and collection of baseline data (Time 1), each participant is randomly allocated (1:1) to either the intervention or control arm. Randomisation is performed separately for each site and stratified by severity of dementia (mild vs. moderate). Randomisation is performed by computer-generated random permuted blocks of varying size provided by [name] [47]. Opaque sequentially numbered envelopes are used to ensure allocation concealment. Participants are not blinded to group allocation, but assessors and statisticians are. Participants are notified by phone and the importance of blinding is explained. Ethics principles are applied to ensure that participants are supported in this process and understand the blinding processes and potential consequences. The members of the research team responsible for data collection from people with dementia and carers, data entry and analysis will remain blind until completion of the main analysis. Unblinding is permissible for the person who is collecting a monthly carer diary as it may contain information about I-HARP service. This will not contaminate the data to be collected as the information is supplied by the carer.

### Methods: data collection, management, analysis, and quality assurance

#### Data collection and management

As shown in Fig. 2, study outcome measure data are collected at 3 assessment times: Baseline /Time 1 at 0 weeks, Time 2 at 20 weeks and Time 3 at 52 weeks. Data are managed using a REDCap electronic database, which is a secure, web-based application designed to support data capture for research studies. The system provides: 1) an intuitive interface for validated data entry; 2) audit trails for tracking data manipulation and export procedures; 3) automated export procedures for seamless data downloads to common statistical packages; and 4) procedures for importing data from external sources. All electronic data are stored in password-protected, secure computer servers/systems and paper records are stored in locked filing cabinets in access-controlled facilities. All data entries are completed via a password-protected validated encrypted study electronic case report form. Only de-identified information is uploaded to the database.

Information collected during the delivery of the intervention (e.g., case notes, case conference notes, audio records of interventions, completed visit checklists) are uploaded to the University of Sydney endorsed secure website. Each site is allocated their own secure folder for use and the interventionists are given clear instructions not to enter any participant’s personal information and to refer to participants only using their participant ID in all their communications and when transcribing information. The project team ensures that the privacy, security and ownership of the research data is maintained, and the data will not be stored or accessible by another organisation without prior ethics approval.

In compliance with the NSW State Records Act, the archiving period for clinical research records will be 15 years (NSW supplement to the National Statement, section 3.3.11). At the conclusion of the archiving period we will consult with the University of Sydney Archives and Records Management Service for advice on the most appropriate manner of destruction and disposal of the research data. Further details about data security and management can be provided by the principal investigator ([name]) on request.

#### Data analysis plan

Each indicator of the implementation outcomes will be analysed using descriptive and inferential statistics as well as qualitative content analysis. All analyses of RCT outcomes will be by intention-to-treat (i.e. including all participants, as randomised, regardless of protocol adherence). The primary analysis of the primary outcome (using the DAD) and secondary outcomes will be an unadjusted comparison between intervention and control groups at Time 2 (short-term effect) and Time 3 (longer-term effect) using two sample t-tests of the change from baseline, or Mann-Whitney tests for outcomes that are not normally distributed. Secondary analyses will use linear regression to adjust for the baseline value of that outcome, stratification variables (site and severity of cognitive impairment) and other covariates (age and pension status).

Qualitative field notes and interview data will be fully transcribed and entered into NVivo 11 (qualitative data analysis software package) for analysis. Two-stage data analysis will be conducted: analysis of the field notes and study findings (quantitative data) followed by qualitative content analysis of interviews with research participants (n ≈ 100) and I-HARP interventionists and participating site managers (*n* = 16–24) to explore their perspectives on reablement approaches to care and I-HARP processes, and mechanisms of their decision making.

The economic evaluation of I-HARP involves costing the intervention itself (e.g. clinicians’ training time, delivery, travel, supervision, care coordination time, minor home modification/assistive devices, intervention materials) and any change in carer workforce participation and health-related client costs over the 52-week period (medications, allied health services, community/aged care, visits to specialists, GPs, hospitals). By combining these cost data with outcome data, relating to mortality and health-related quality of life (using the EQ-5D-5 L), a cost-utility analysis will be undertaken, reporting a cost per quality-adjusted life year (QALY) of the I-HARP intervention relative to controls. The economic evaluation will present both a ‘within-trial result’ (i.e. considering only those costs and outcomes accruing over 52 weeks) as well as to be extrapolated over a longer time period, such as ten years. As we will have 52 weeks of participant-level data, we will apply bootstrapping methods to estimate the uncertainty around cost-effectiveness figs. [48].

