### Methods: study sites, participants, intervention, outcomes and randomisation

#### Sites and sample size

We are recruiting participants across three public hospitals (two of the hospitals are combined into one research site as they have a common geriatric service) and two community aged care providers in the Sydney metropolitan area, New South Wales, Australia. A sample of 128 dyads will give 80% power at the 2-sided 5% significance level to detect a medium effect size of 0.5 between control and intervention groups on the primary outcome assessed at Time 2 (20 weeks, short term effect) and Time 3 (52 weeks, longer term effect). An effect size of 0.5 is clinically relevant as it implies that a trained observer can detect a difference between a control and intervention group in a specified outcome [37], in our case functional independence using the Disability Assessment for Dementia (DAD). We are confident that it is achievable as our pilot study showed a larger effect size of 0.61, as did a similar study of CAPABLE [21]. To allow for 25% loss to follow-up, 170 eligible dyads will be recruited. Based on consultations with the research site partner organisations, we estimated over 500 clients would be potentially eligible for I-HARP from the 4 research sites over 6 months, and a 35% participation rate (based on our previous community trials) would provide 175 dyads. However, current recruitment rates suggest an extra 12 months will be needed to meet the target sample size.

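### The analysis is described as including everyone randomised, but the primary change-score test can use only dyads with a follow-up DAD and does not adjust for baseline

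*Protocol article*

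**What the plan says.** The Data analysis plan states that all trial outcomes are analysed by intention-to-treat, glossed as "including all participants, as randomised, regardless of protocol adherence". The primary analysis is an unadjusted comparison at Time 2 and at Time 3, "using two sample t-tests of the change from baseline, or Mann-Whitney tests for outcomes that are not normally distributed". Baseline adjustment comes second: "Secondary analyses will use linear regression to adjust for the baseline value of that outcome", together with site, severity, age and pension status.

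The Assessment section fixes the primary time point: "The primary outcome is the client’s functional independence at Time 2", which is 20 weeks. DAD is measured at baseline, 20 weeks and 52 weeks.

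Under Sites and sample size: "A sample of 128 dyads will give 80% power at the 2-sided 5% significance level to detect a medium effect size of 0.5". Then: "To allow for 25% loss to follow-up, 170 eligible dyads will be recruited". That single allowance covers both follow-up times. The Retention section lists steps to limit loss, including assessment after a move to a nursing home. The article does not say how a missing DAD is treated in the primary test.

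**The concern.** A change from baseline does not exist for a dyad with no follow-up value. The t-test and its Mann-Whitney alternative therefore leave that dyad out, whichever arm it was allocated to. The sentence promising that everyone randomised is included and the test named straight after it cannot both hold, unless missing values are filled in by a step that the article does not mention.

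Two things are at stake. The first is description: a result from those with outcome data would be reported as covering everyone randomised. The second is the estimate. An unadjusted change score is sensitive to who remains, because people who start high tend to fall back and people who start low tend to rise. If the link between baseline function and loss differs by arm, that regression to the mean enters the treatment comparison. Participants know their allocation, and one arm receives a programme of home visits and carer sessions while the other has usual care and vouchers. A difference in who is lost is therefore plausible, though nothing in the article shows it.

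**Working it through.** **1. The plan's own sample size.** Inputs from Sites and sample size: effect 0.5 SD, two-sided 5%, 80% power, 25% loss. Allocation: "each participant is randomly allocated (1:1) to either the intervention or control arm".

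- The two-sample t-test needs 63.8 per arm, rounded up to 64, so 2 × 64 = 128. Power at 64 per arm is 80.1%. The figure of 128 reproduces.
- Allowing for loss: 128 / 0.75 = 170.7, against 170 stated. This reproduces to rounding.

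**2. Who the test uses.**

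- With data: 170 × 0.75 = 127.5. Without: 170 × 0.25 = 42.5, so about 42 dyads.
- Power at effect 0.5 is 80.0% on 127.5 dyads and 90.0% on all 170. The stated 80% is therefore the power of a test on those with data.
- The abstract gives 176 dyads. On that figure 176 × 0.75 = 132 have data, with power 81.4%. The conclusion is the same.

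**3. When the change score is biased.** Assumptions, none from the article: no true effect; baseline and follow-up DAD with SD 1 and correlation rho; equal loss rates in the two arms; loss in controls rising as baseline DAD falls (logistic slope −1 per SD); loss in the intervention arm unrelated to baseline.

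The expected change given baseline b is −(1 − rho) × b. Remaining intervention participants have mean baseline 0. Remaining controls have mean baseline m above 0, so their expected change is −(1 − rho) × m, and

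bias (intervention minus control) = (1 − rho) × m.

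Numerical integration gives m = 0.212 at 25% loss and 0.090 at 10%.

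| Loss per arm | rho | Bias of unadjusted change score |
|---|---|---|
| 25% | 0.7 | 0.3 × 0.212 = 0.064 SD |
| 10% | 0.7 | 0.3 × 0.090 = 0.027 SD |
| 25% | 0.5 | 0.5 × 0.212 = 0.106 SD |
| 25% | 0.8 | 0.2 × 0.212 = 0.042 SD |

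Simulation with 85 per arm agrees: 0.06 SD at 25% loss and 0.03 SD at 10% (rho 0.7). Regression on baseline gives a bias of about 0 in the same trials. When the same loss mechanism acts in both arms, the change-score bias is also about 0.

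**4. Scale.** Against the 0.5 target, 0.064 / 0.5 = 13% and 0.027 / 0.5 = 5%. In this scenario the bias favours the intervention. The standard error of one trial's change-score estimate is about 0.136 SD at 25% loss, so 0.064 / 0.136 = 0.47, or just under half a standard error.

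**5. What baseline adjustment would not cure.** If loss depends on the unseen outcome, rates matter too. Suppose 20% are lost in one arm and 30% in the other, and the changes of those lost are worse by k SD than those of people who remain. The difference then shifts by (0.30 − 0.20) × k: 0.05 SD at k = 0.5 and 0.10 SD at k = 1.0. With 25% lost in each arm and the same k, the shift is 0. These figures are also assumptions.

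**The case against.** The strongest reply is that the intention-to-treat phrase is about analysis by allocated arm with nobody removed for poor adherence. Its closing words on adherence support this, as does the Retention section, which keeps clients in the study when their dementia progresses. That part of the plan is sound. What remains is the claim that all participants are included, which the named test does not meet.

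Second, this is a condensed article. A statistical analysis plan may add imputation before the t-test, and missing-data detail commonly sits there. This stands: the absence of an imputation method, a sensitivity analysis or a rule for deaths is not a finding. The order of the analyses is fixed here, however, with the unadjusted change score first.

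Third, the regression already planned as secondary adjusts for baseline and removes the bias in the scenario above. This stands too, and it makes the remedy cheap. It also means that most of the gain comes from baseline adjustment. The gain from using Time 3 for those missing at Time 2 may be small, since many of them will also be missing at 52 weeks.

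Fourth, 25% is one allowance covering both times. Loss by 20 weeks may be lower, and differential loss is assumed. Vouchers for controls, cards and gifts for everyone and monthly calls to all carers work against it. This limits the size of the point.

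A reader might infer that the primary result must be biased, or that the trial has no intention-to-treat analysis. The article supports neither.

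**Conclusion.** The point holds as a mismatch between the stated analysis set and the named test, together with a choice of primary method that is weaker than one already in the plan. As written, the primary analysis compares dyads with outcome data according to their randomised arm. The sample size confirms this: 80% power belongs to about 128 of 170 dyads.

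The possible bias is modest and conditional. It is about 0.06 SD at 25% loss and 0.03 SD at 10%, at a correlation of 0.7 and with loss tied to low baseline DAD in controls only. It is about zero if the loss mechanism is the same in both arms, and about zero after baseline adjustment when loss depends only on baseline and arm. Certain bias, or a loss of as many as 42 dyads at the 20-week primary time, cannot be read from the article. The change is worth making because it is cheap and uses data already being collected.

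**What to change.** Make the primary analysis a likelihood-based model of DAD at Times 1, 2 and 3 in all randomised dyads. Baseline enters as a response with a common mean in the two arms, the covariance is unstructured, and site and severity are covariates. Take the Time 2 contrast as primary and the Time 3 contrast as secondary.

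At the least, promote the planned baseline-adjusted regression to primary and move the unadjusted t-test or Mann-Whitney test to a supporting role. The regression still needs a follow-up value, so this option does not make the present intention-to-treat sentence true.

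Under either option, reword that sentence. With the longitudinal model it can say that all randomised dyads contribute their available DAD values in their allocated arm. With the regression it should say that participants with outcome data are analysed as randomised.

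The cost is a change of wording and slightly more analysis, with no new data. The model assumes missing at random, which a sensitivity analysis can probe. The details of that analysis, and the handling of deaths, can sit in the statistical analysis plan. The change should be fixed before unblinding.

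### The primary analysis is a valid but less precise unadjusted change-score test; the baseline- and stratum-adjusted regression already planned as secondary should be made primary

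*Protocol article*

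**What the plan says.** All references are to the protocol article.

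- **Data analysis plan, primary analysis.** For the Disability Assessment for Dementia (DAD) and the secondary outcomes, the primary analysis "will be an unadjusted comparison between intervention and control groups at Time 2 (short-term effect) and Time 3 (longer-term effect"). The method named is a t-test on change scores, with a Mann-Whitney test where normality fails.
- **Data analysis plan, secondary analysis.** "Secondary analyses will use linear regression to adjust for the baseline value of that outcome, stratification variables (site and severity of cognitive impairment"), together with age and pension status.
- **Randomisation, allocation concealment, and blinding.** Allocation is 1:1, using "computer-generated random permuted blocks of varying size". "Randomisation is performed separately for each site and stratified by severity of dementia (mild vs. moderate"). With four research sites (Sites and sample size) and two severity levels, that makes eight strata.
- **Sites and sample size.** 128 evaluable dyads are planned for 80% power at the two-sided 5% level and an effect size of 0.5. The section does not say whether that effect is in SDs of the DAD score or of its change.

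The article gives no reason for leaving baseline and the stratification factors out of the primary analysis.

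**The concern.** Two features of the primary test cost precision.

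**Baseline.** A change score fixes the coefficient of baseline DAD at 1. Regression estimates that coefficient from the data, and in large samples it is never less precise. It also corrects for a chance difference between the arms at baseline.

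**Strata.** Permuted blocks within site and severity keep the arms close to balanced in each stratum. If those factors predict change in DAD, a standard error that ignores them still counts variation that the design has removed. The interval is then too wide and the test rejects less often than its nominal 5%.

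What is at stake is the chance of missing a real benefit. The trial is sized at 80% power with no margin, allows for 25% loss, and reports that recruitment needs an extra 12 months. The more precise analysis is already in the plan, but the confirmatory conclusion rests on the other one.

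**Working it through.** **Inputs from the protocol article.** 128 evaluable dyads (64 per arm at 1:1), effect size d = 0.5, two-sided 5%, 80% power.

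**Assumed inputs, not in the article.** Correlation rho between baseline and Time 2 DAD; ratio k of the Time 2 SD to the baseline SD; share R² of the variance in *change* explained by site and severity.

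**1. The plan's own figure.** A two-sample t-test with d = 0.5, two-sided 5% and 80% power needs 63.8, so 64 per arm, or 128 in total. The exact power is 80.1%. The stated 128 is reproduced and fits the planned test if 0.5 is in SDs of change.

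**2. Gain from baseline adjustment.** Within arms, the ratio of the adjusted variance to the change-score variance is

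k²(1 − rho²) / (1 + k² − 2k·rho), which reduces to (1 + rho)/2 when k = 1.

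The effective effect size is 0.5/√ratio. Power is from the noncentral t with 64 per arm; strata are not used here.

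| rho | k | Variance ratio | Effective d | Power |
|---|---|---|---|---|
| change score | – | 1 | 0.500 | 80.1% |
| 0.5 | 1.0 | 0.750 | 0.577 | 90.0% |
| 0.7 | 1.0 | 0.850 | 0.542 | 86.1% |
| 0.8 | 1.0 | 0.900 | 0.527 | 84.1% |
| 0.7 | 1.2 | 0.7344/0.76 = 0.966 | 0.509 | 81.5% |
| 0.8 | 1.2 | 0.5184/0.52 = 0.997 | 0.501 | 80.3% |

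The direction does not depend on these assumptions. In units of the baseline variance, the change score exceeds the adjusted estimator by (1 − k·rho)², which is never negative and is zero only when k·rho = 1.

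**3. If d = 0.5 is in SDs of the raw DAD score.** With k = 1, the change-score effect is 0.5/√(2(1 − rho)) and the adjusted effect is 0.5/√(1 − rho²).

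| rho | Change-score power | Adjusted power |
|---|---|---|
| 0.3 | 66.0% | 83.7% |
| 0.5 | 80.1% | 90.0% |
| 0.7 | 95.2% | 97.6% |

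On this reading the planned test falls below 80% when rho is below 0.5, and the gain is only 2.4 points at rho 0.7.

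**4. Effect of ignoring the strata.** With arms balanced within strata, the true standard error is √(1 − R²) times the unadjusted one. So the unadjusted standard error is too large by 1/√(1 − R²) − 1, and the true two-sided error is 2(1 − Φ(1.96/√(1 − R²))).

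| R² of change | Standard error too large by | True two-sided error |
|---|---|---|
| 0 | 0% | 5.0% |
| 0.05 | 2.6% | 4.4% |
| 0.10 | 5.4% | 3.9% |
| 0.20 | 11.8% | 2.8% |

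**5. Both together, by simulation.** The setting was 128 participants, eight strata, permuted blocks of 2, 4 or 6 (block sizes assumed), rho 0.7, k = 1 before stratum effects, R² 0.10 and 6,000 runs. The unadjusted t-test had type I error 4.1% and power 81.6%. Regression on arm, baseline and strata had 5.3% and 89.3%.

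**The case against.** The strongest reply is that nothing in the plan is invalid, and most of it stands.

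- **Validity.** Under randomisation the change-score test is unbiased, and ignoring the strata makes it conservative. A reader might infer that regression to the mean biases the result or that false positives are inflated. Neither follows: the expected baseline difference is zero, and the error rate is at or below 5%.
- **Planned power.** A reader might infer that the trial is underpowered. The article does not support that. The stated 128 gives the planned test its 80% if d is in SDs of change. Only the raw-score reading with rho below 0.5 takes it under 80%, and the article does not say which SD is meant.
- **Size of the gain.** The formula (1 + rho)/2 needs equal SDs at both times. The article gives neither rho nor k, and a larger follow-up SD can remove nearly all the gain.
- **Strata.** Site and severity may mainly predict the level of DAD, and subtracting baseline already removes stable level differences. Only their share of the variance in change counts. If they do not predict change, the calibration point vanishes.
- **Baseline imbalance.** A chance imbalance of 0.2 SD moves the change-score estimate by 0.06 SD at rho 0.7 and equal SDs, because (1 − 0.7) × 0.2 = 0.06. This is the same loss as the variance in step 2 seen another way, and must not be added to it.
- **Already available.** The adjusted estimate will be produced anyway, and naming one analysis as primary settles in advance which one governs.

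These points limit the size and urgency of the concern. They do not give a reason to prefer the less precise analysis as primary.

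**Conclusion.** The point holds as a recommendation for better precision. The planned primary test is valid, prespecified and conservative, and its sample size is consistent with it on the change-score reading. It gives up precision that the trial's own design and planned regression would supply.

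The direction is firm. The size is conditional on figures that the article does not give. With equal SDs, power rises from 80.1% to about 84% to 90% for rho from 0.8 down to 0.5. With a follow-up SD 1.2 times the baseline SD, the variance falls by only 3% at rho 0.7 and 0.3% at rho 0.8. The stratum effect runs from nothing to a standard error about 12% too large, over an assumed R² of 0 to 20% of the variance in change. This is a free improvement, recommended but not mandatory.

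**What to change.** Before unblinding, exchange the roles of the two analyses:

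- **Primary:** linear regression of DAD at Time 2 on arm, baseline DAD, site and the mild or moderate stratum as randomised.
- **Secondary scales:** the same model, each with its own baseline value.
- **Sensitivity:** the unadjusted t-test of change, or the Mann-Whitney test for clearly non-normal outcomes.

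The cost is a short dated amendment to the data analysis plan. No further participants, visits or measurements are needed, since baseline value, site and severity are already collected for the planned regression. The article keeps the analysts blind until the main analysis is complete, so the change can be made cleanly now. After unblinding it would look data-driven.

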Aligned with the I-HARP theoretical framework in Fig. 1, our hypotheses (HP) are that, compared to the usual care control group, the I-HARP group will have:At 20 weeks:HP1 improved functional independence (primary outcome);HP2 enhanced quality of life;HP3 improved mobility;HP4 reduction in depressive symptoms;HP5 improved carer quality of life;HP6 decreased carer burden; and HP7 improved home environment safety.At 52 weeks:HP8 the benefits (HP1-HP7) will be sustained; andHP9 I-HARP will lead to decreased total health care costs.

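### The t-test or Mann-Whitney rule also covers 52-week health care costs, where it does not fit: there is no baseline to subtract, and a rank test does not compare mean or total cost

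*Protocol article*

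**What the plan says.** In the Data analysis plan of the protocol article, one sentence governs the unadjusted analyses. Its scope is "The primary analysis of the primary outcome (using the DAD) and secondary outcomes will be an unadjusted comparison" at Time 2 and Time 3, and its method is a two-sample t-test on change from baseline, "or Mann-Whitney tests for outcomes that are not normally distributed". No outcome is exempted, and no criterion for non-normality is given.

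The Assessment section lists "total health care costs over the 52 weeks following randomisation" among the secondary outcomes. The Phase I hypotheses include HP9, for 52 weeks: "I-HARP will lead to decreased total health care costs".

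The economic paragraph of the Data analysis plan describes a cost-utility analysis on participant-level data, for which "we will apply bootstrapping methods to estimate the uncertainty around cost-effectiveness" figures. It names no test or interval for the cost difference in HP9. It lists the cost of delivering the programme separately from clients' health-related costs, and HP9 does not say whether the programme cost counts.

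For the primary outcome, Sites and sample size states: "A sample of 128 dyads will give 80% power at the 2-sided 5% significance level to detect a medium effect size of 0.5". That is a standardised difference in means.

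**The concern.** Both branches of the rule misfit the cost outcome. The t-test branch needs a change from baseline, but the outcome is a sum that starts at randomisation, and no matching pre-randomisation period is defined. A Time 2 comparison of a 52-week total has no meaning either. Costs that include hospital stays are usually right-skewed, so the other branch would apply. Mann-Whitney then asks whether a randomly chosen I-HARP client tends to cost more than a randomly chosen control. HP9 asks whether total cost falls, which is a question about the mean.

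The two questions can have opposite answers when a programme adds a moderate cost to everyone and prevents a few expensive events. That pattern is plausible here: each I-HARP client receives home visits, carer sessions and up to A$1000 of modifications or devices. The trial could then report a rank test for HP9 that contradicts the mean costs in its own cost-utility analysis.

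The same clause leaves the primary DAD comparison to be a mean difference or a rank comparison, depending on the distribution observed.

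**Working it through.** **1. The plan's own figure.** For d = 0.5, two-sided 5% and 80% power, the exact two-sample t-test needs 63.8, so 64 per arm or 128 dyads, with power 80.1%. The stated 128 reproduces, and it rests on a difference in means.

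**2. What each test compares.** The t-test compares E(I-HARP cost) with E(control cost). Mann-Whitney tests whether P(I-HARP cost > control cost) = 0.5, counting ties as half. For skewed distributions of different shape, neither follows from the other.

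**3. Cost simulation.** The protocol gives no costs, so every input here is an assumption: 64 per arm; base cost lognormal (log-SD 0.8); admission cost lognormal with mean A$40,000 (log-SD 0.6); a fixed programme cost for every I-HARP client; 4,000 trials per row.

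Mean cost = base + P(admission) × 40,000 + programme cost.

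Example: control 8,000 + 0.25 × 40,000 = 18,000; I-HARP 8,000 + 0.15 × 40,000 + 4,000 = 18,000.

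The last two columns give the percentage of trials in which I-HARP was declared significantly costlier. By chance alone, about 2.5% is expected when the means are equal.

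| Base (A$) | Admissions, control to I-HARP | Programme cost (A$) | True mean difference (A$) | Mann-Whitney | Welch t-test |
|---|---|---|---|---|---|
| 8,000 | 25% to 15% | 4,000 | 0 | 56.6% | 3.0% |
| 8,000 | 30% to 20% | 4,000 | 0 | 43.2% | 2.4% |
| 8,000 | 20% to 10% | 4,000 | 0 | 69.8% | 3.2% |
| 8,000 | 45% to 35% | 4,000 | 0 | 16.4% | 2.4% |
| 20,000 | 25% to 15% | 4,000 | 0 | 11.8% | 2.6% |
| 25,000 | 25% to 15% | 4,000 | 0 | 8.1% | 2.8% |
| 8,000 | 25% to 15% | 3,000 | −1,000 | 33.6% | 1.3% |
| 20,000 | 25% to 15% | 3,000 | −1,000 | 5.0% | 1.8% |
| 8,000 | 25% to 15% | 0 | −4,000 | 0.2% | 0.1% |

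Repeat runs of the equal-mean rows with base costs of A$20,000 to A$25,000 gave about 7% to 12%. In the last row the tests agree: Mann-Whitney found I-HARP cheaper in 15.3% of trials and Welch in 18.4%.

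**4. A second set of assumptions.** Gamma base cost (mean 8,000), gamma admission cost (mean 30,000), admissions 30% to 10%, programme cost 4,000. The means by arithmetic are 8,000 + 4,000 + 0.10 × 30,000 = 15,000 for I-HARP and 8,000 + 0.30 × 30,000 = 17,000 for control. In a large simulated sample the I-HARP mean was lower (15,027 against 17,009), its median was higher (11,434 against 9,758), and P(I-HARP cost > control cost) was 0.56. Rank and mean point in opposite directions.

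**5. Primary outcome.** Shapiro-Wilk at 5% on residuals was assumed as the switching rule, with 64 per arm and 5,000 trials. Type I error of the two-stage rule was 4.7% with normal data and 4.4% with gamma data. With normal data and d = 0.5, power was 79.8% for both the two-stage rule and the fixed t-test. If Mann-Whitney were always used on normal data (relative efficiency 0.955), power would be that of 64 × 0.955 = 61.1 per arm, or 78.3%.

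**The case against.** The strongest reply is that the rule was never meant for costs. It is written as a change from baseline at two visits, which a 52-week total cannot supply. The economic paragraph under the same heading handles participant-level costs, and an incremental cost per QALY needs the difference in mean costs. On this reading only a cross-reference is missing. The intention is plausible, and it confines the defect to the HP9 comparison; the cost-utility analysis itself is not affected. But the text covers all secondary outcomes, lists costs among them and exempts none, and the economic paragraph gives HP9 no comparison of its own. A normality criterion in an unseen analysis plan would not help, because a clear criterion would still send skewed costs to the rank test.

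The second reply is that the size rests on invented costs. This stands. A reader might take the 56.6% row as the likely error rate. The documents do not support that: a higher base cost, plausible for clients of aged care services, brings it to about 10%, and leaving out the programme cost removes the reversal.

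Third, a reader might infer that the primary result is compromised. It is not. Error rates barely move, the statisticians are blinded to allocation, and the planned adjusted linear regression gives a mean difference in any case, although as a secondary analysis.

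**Conclusion.** The concern holds for costs. As written, HP9 falls under a rule that has no baseline to work with and would probably lead to a test of a different question. That a rank test can disagree with the mean does not depend on the particular figures assumed; how often it would mislead does. With equal true means and the programme cost included, Mann-Whitney called I-HARP costlier in roughly 7% to 70% of simulated trials, against about 2% to 3% for a comparison of means. With the programme cost excluded there was no reversal, and HP9 leaves open which definition applies. It cannot be concluded that the trial will report costs in the wrong direction.

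For the DAD the point is minor. The effect measure should not depend on the observed distribution, but type I error and power are practically unchanged.

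**What to change.** Exempt total health care costs from the t-test or Mann-Whitney rule. Define HP9 as the difference between arms in mean 52-week cost per participant, with a bootstrap interval and no change from baseline. State whether the programme cost is included, or report both versions. Bootstrapping is already planned for the cost-utility analysis, so this costs only wording. The price is a wide interval for the mean difference.

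For the DAD, name the mean difference in change from baseline at Time 2 as the primary effect measure whatever the distribution, consistent with the d = 0.5 sample size and the adjusted regression, and keep the rank test as a sensitivity analysis. The 128 evaluable dyads and 80.1% power are unchanged. Neither change affects data collection or trial conduct.
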